#### Secondary outcome measures

Mean group scores of every condition will be calculated for all secondary measures. Secondary outcome measures assess diverse constructs at pre-test (t_0_), post-test (t_2_), and follow-up test (t_3_), hence allowing us to compare changes within and between conditions from pre- to post-test and from pre- to follow-up test. Children’s HRQoL is assessed using the KINDL-R questionnaires for parents and children. Parents’ satisfaction with as well as their expectations about the intervention’s effects are assessed using the FERT questionnaire [57]. Children’s mathematics, reading, and writing skills are assessed using the LVD-M 2–4 [68] and the SLRT-II [79]. Children’s self-control and academic self-efficacy are assessed using the SCS-K-D and a scale by Schwarzer and colleagues [54] in both a version for parents and one for their children. Executive functioning is furthermore assessed using a digit span task [64] (verbal working memory), the Corsi Block Tapping Task [62] (visuo-spatial working memory), and the BRIEF [56], a questionnaire handed out to parents and teachers. Sustained attention is assessed using the Conner’s Continuous Performance Test [61, 67], and response inhibition is assessed using the Stop-Signal Task [80]. General cognitive ability is assessed using the matrix span task [64]. Moreover, activity data are collected with actigraphs measuring acceleration on the vertical, horizontal, and perpendicular axes with a range of −6 to +6 g (g = gravitational force). Heart rate variability, as calculated from the ECG, as well as the motivation for every training session, as assessed with a self-report questionnaire for the children, serve as secondary outcome measures.

#### Statistics

##### Calculation of the sample size

The sample sizes for the two analytical approaches were calculated using G Power version 3.1.9.2. Firstly, we calculated the sample size that is required in order to yield a significant effect of treatment within conditions. We expect appropriate effect sizes to range between those known for within and between designs, hence expecting an effect size of *ES* = .69 [26] with a predefined α of .05 and a power of at least .80. Using a one-tailed *t* test due to directed hypotheses, the study requires at least 15 subjects per group, assuming a post- versus pre-effect, or at least 27 subjects, assuming treatment versus passive waiting control group effect. Secondly, we calculated the sample size that is required for a repeated measures analysis of variance (ANOVA) with three groups and two measurement dates in order to be able to detect effects of at least small to medium effect sizes. Hence, assuming an *ES* of .35, a predefined α of .05, a power of at least .80, and a correlation of .5 between repeated measures results in a total sample size of 84, that is, 28 per group. Consequently, taking into consideration the results of our first and second analyses, we aim for 30 participants per group.

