### Interventions

Two conditions involve 15 sessions of a NIRS-based NFT, one in a VR classroom setting and one in a 2D classroom setting to control for specific effects of trainings in VR and 2D. The third condition involves an EMG-based BFT in VR and constitutes a control condition that allows the evaluation of effects that are uniquely attributable to the NFT itself.

Every training session lasts approximately 60–70 min including a preparation phase at the beginning (20 min), in which the NIRS cap and optodes are fitted to the head, or the EMG electrodes are placed on both musculi supraspinatus and both mastoids. For the participants in the VR classroom setting, the head-mounted display (HMD) is mounted. The training sessions also include the NFT or BFT (45 min) and a training phase with stimulus cards at the end of the training sessions 6–15 (5 min). The stimulus cards present a screenshot of the 2D screen. Within the laboratory setting, these cards are introduced as cue stimuli associated with brain activation or increased muscular activity of the musculi supraspinatus as learned during the NFT or BFT. When employed at home, they are thought to facilitate activation and to establish an association between, for instance, doing homework and brain or muscle activation [44].

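### The sample-size section claims 80% power for small to medium effects, but 84 to 90 children give 80% power only for arm differences of roughly 0.7 to 0.9 SD of change

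*Protocol article*

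**What the plan says.** The Protocol article, section Calculation of the sample size, gives two calculations.

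- The first takes ES .69 at 5% alpha and 80% power. The test is directional: "Using a one-tailed *t* test due to directed hypotheses". For change within a group the result is 15 children per group. For a comparison between groups the figure is 27, and the wording shows which comparator was meant: "or at least 27 subjects, assuming treatment versus passive waiting control group effect".
- The second is a repeated-measures ANOVA with three groups and two occasions, done "in order to be able to detect effects of at least small to medium effect sizes". With ES .35, alpha .05, power .80 and a correlation of .5 it "results in a total sample size of 84, that is, 28 per group". The metric of .35 (f, d or other) and the term tested (group, time or their interaction) are not stated.

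Citing both calculations, the section sets the target at 30 per group.

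The section Interventions describes three trained arms: "The third condition involves an EMG-based BFT in VR and constitutes a control condition". Under Hypotheses, the second hypothesis sets neurofeedback against EMG biofeedback, and the third sets VR against 2D neurofeedback. The analysis section plans repeated-measures ANOVA with post hoc tests.

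**The concern.** Two of the four hypotheses are differences between active treatments. The section Control conditions for NFT studies expects neurofeedback and biofeedback to have similar behavioural effects, with a larger total effect for neurofeedback because of its specific component. A reader who wants to know whether the trial can show that extra component, or the added value of VR, will rely on the statement about small to medium effects.

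If the number behind that statement corresponds to a large arm difference, a non-significant result on hypothesis 2 or 3 would appear to come from an adequately powered comparison when it did not. The 27 per group adds to this impression, because an effect measured against untreated children is cited in support of a trial in which every child is trained.

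**Working it through.** **Inputs.** From Calculation of the sample size: ES .69 (one-tailed t test), ES .35, alpha .05, power .80, correlation r = .5, k = 3 groups, m = 2 occasions. From Randomization: 30 per arm, N = 90. Power is from the exact noncentral t and F distributions.

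**1. The plan's t-test figures.** ES .69, one-tailed: paired n = 15 (power .815); two-sample n = 27 per group (power .804). Both reproduce.

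**2. The plan's ANOVA figure.** The test has 2 and N − 3 degrees of freedom, and N rises in multiples of 3.

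| Reading of .35 | Noncentrality | N for 80% power |
|---|---|---|
| f = .35, interaction, raw-SD formula | f²·N·m/(1 − r) = 0.49·N | 24 |
| f = .35, between groups, raw-SD formula | f²·N·m/(1 + (m − 1)r) = 0.1633·N | 63 |
| f = .175, interaction, raw-SD formula | 0.030625·4·N = 0.1225·N | 84 (power .812) |
| f = .35, change-score scale | f²·N = 0.1225·N | 84 (power .812) |

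The last two rows are the same calculation: at N = 84 both have noncentrality 0.1225 × 84 = 10.29. The raw-SD interaction effect is half the SD of the three mean changes. At r = .5 the SD of change, √(2(1 − r)), equals the raw SD. So f = .175 means that the mean changes have an SD of .35.

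**3. What .35 means as a difference between arms.** Let D be the largest difference in mean change, in SDs of change.

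- Two arms equal, one apart: the SD of the three means is D·√2/3, so D = 3 × .35/√2 = 0.74.
- Evenly spaced arms: the SD of the means is D/√6, so D = .35 × √6 = 0.86.

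**4. Smallest differences with 80% power.**

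- Omnibus, N = 84: f = .345, so D = 0.73 to 0.85.
- Omnibus, N = 90: f = .333, so D = 0.71 to 0.82.
- Two arms, 30 each, two-sided (noncentrality d·√(30/2), 58 df): 0.74.
- Both neurofeedback arms pooled against EMG, 60 against 30 (noncentrality d/√(1/60 + 1/30)), two-sided: 0.63.

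**5. Power for smaller differences at 30 per arm.**

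| Arm difference (SD of change) | Pairwise two-sided | Pairwise one-sided | Omnibus, N = 90 |
|---|---|---|---|
| 0.35 | 27% | 38% | 20–26% |
| 0.50 | 48% | 61% | 38–49% |

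**6. ES .69 at 30 per arm.** Power is 84% one-tailed and 75% two-tailed.

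**7. Sensitivity to the correlation.** The unit is the SD of change. Suppose, as a favourable assumption, that the pre-post correlation were as high as the retest value of about .85 quoted for the Conners 3. The SD of change would then be √(2 × .15) = 0.548 raw SD, and 0.74 to 0.86 SD of change would be about 0.41 to 0.47 raw SD.

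**The case against.** The strongest defence is that nothing is miscalculated. All three figures reproduce, and one coherent reading uses every stated input: .35 is midway between the conventional small and medium values of d (.20 and .50), half of it is f = .175, midway between the small and medium values of f (.10 and .25), and that input gives exactly 84. On the f scale the label then fits nominally. This stands, and a reader who infers an arithmetic error would be wrong. It does not settle the point, because the same input still requires arms 0.74 to 0.86 SD apart in mean change, and the article does not tell the reader so.

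A reader might also infer that the article promises 80% power for an arm difference of 0.35 SD. It does not say that; the metric is simply missing. The 27% shows what follows if the unlabelled .35 is taken as a standardised difference, as its place beside the t-test ES of .69 invites.

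The 27 per group does not set the sample size; 28 rounded up to 30 does. The one-tailed test is disclosed and the hypotheses are directional, so the documents do not support treating it as a mistake or requiring 34 per group, the two-tailed figure. What remains is that the comparator behind the 27 is absent from the trial.

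Three mitigating facts also stand: a higher pre-post correlation shrinks the detectable raw-scale difference; pooling the neurofeedback arms helps hypothesis 2 (0.63 SD), though not VR against 2D; and change within arms, which hypothesis 1 concerns, is better powered (80% power for about 0.53 SD of change at 30 children, two-sided).

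**Conclusion.** The concern holds as a fault in the power statement: the metric is missing and the label does not fit the contrasts of interest. At the protocol's own r = .5, both readings that yield 84 correspond to a largest arm difference of 0.74 to 0.86 SD of change. With 90 children analysed, the 80%-power minimum is 0.71 to 0.82 SD (omnibus), 0.74 SD (two arms, two-sided) or about 0.63 SD (pooled neurofeedback against EMG). A pairwise difference of 0.50 SD has roughly even odds of detection, and 0.35 SD about one in four.

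These figures assume equal arms, complete data, alpha .05 without multiplicity adjustment, and analysis of change between two occasions.

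Two further inferences go beyond the document. One is that 90 children are too few: the article states no smallest arm difference of interest against which to judge that. The other is a specific loss of power from dropout: the article gives no expected rate, so any completer number would be an assumption. Nor does the article say that it will interpret a null contrast as equivalence; the risk lies in how the current wording would be used.

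**What to change.** Keep N = 90 and amend Calculation of the sample size:

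1. State the metric of .35 and the term tested: f = .175 for the group-by-time interaction, or f = .35 on change scores, whichever was entered.
2. Replace the small-to-medium label with text such as: *With 30 children per arm and a pre-post correlation of .5, a two-sided 5% comparison of two arms in change from baseline has 80% power for a difference of 0.74 SD, about 48% for 0.50 SD and about 27% for 0.35 SD; the omnibus group-by-time test has 80% power for a largest difference of 0.71 to 0.82 SD.* If hypothesis 2 will be tested with the neurofeedback arms pooled, add 0.63 SD for that contrast.
3. Keep the t-test figures as a record of how N was chosen, but note that the 27 per group refers to a waiting-list comparison and does not apply to the active-arm contrasts. Add that .69 has 75% power two-sided at 30 per arm.
4. State that a non-significant arm contrast under hypothesis 2 or 3 will not be read as absence of a specific or VR effect.

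The cost is wording only: no extra children and no change to the design or analysis. The downside is that the stated power becomes less favourable.

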##### Data security and storage

All data are acquired and stored using anonymous codes. Codes and corresponding real names are noted on a code list stored in a lockable cupboard that can only be accessed by staff members of the project. The code list will be destroyed after the data collection, including follow-up tests, is finished. All data collected will be deleted after ten years from their first publication. No data monitoring committee is required for this study, as this is not a multicentre study.

## Discussion

We presented an innovative study design and protocol of a randomized controlled trial (RCT) with NIRS-based neurofeedback training in children with ADHD. First, this study aims to investigate the specific effects of NIRS-based NFT compared to effects of EMG-based BFT on children with ADHD. Both variants of the training are conducted in a VR classroom environment. Second, we aim to compare differential effects of NIRS-based NFT in a 2D and a VR environment. Third, this study examines effects of NIRS-based NFT and EMG-based BFT on self-control as well as on school performance of children with ADHD.

There are already promising findings providing evidence for the efficacy of NIRS-based NFT in children with ADHD in the scope of a pilot study [27]. The study presented here now aims to further examine the findings in a comprehensive design. An active control condition receiving an EMG-based BFT will serve to differentiate specific as well as unspecific effects of the interventions. In addition to strong ethical concerns and poor compliance to treatment in NFTs using sham feedback as a control condition [30, 31], a control condition receiving a sham feedback is not adequate to approach this question. NFT and BFT for ADHD treatment generally train self-regulation in different domains [22, 81] in the fashion of an operant conditioning paradigm. On the one hand, participants acquire self-regulation skills that allow control of a specific endogenous parameter, namely brain activation. On the other hand, they learn to self-regulate behavioural conditions such as being attentive, sitting still, and enduring boredom. Therefore, we expect NFT as well as BFT to yield the same degree of effects in the latter domains, while only the acquisition of self-regulation skills related to the specific endogenous parameter will yield unique effects on ADHD symptomatology. Hence, comparing the effects of a NIRS-based NFT in the VR setting and those of an EMG-based BFT in VR in this study will illustrate the proportion of specific effects as well as effects common to both interventions.

With the study design presented, we furthermore aim at examining whether an NFT in a naturalistic VR setting might yield greater effects than an NFT in a 2D setting. From a theoretical point of view, both the acquisition of self-regulation skills in the laboratory and their transfer to everyday life situations (e.g. a classroom setting) might be facilitated by training in a naturalistic VR environment [34]. The VR environment elicits psychological and behavioural responses that would similarly occur in real life [34]. As these responses occur within a therapeutic setting, they provide the starting point for behavioural and psychological interventions [34]. Transfer of skills acquired in the training is furthermore facilitated due to the high degree of realism of the training setting [35]. In addition, training motivation has been identified as an important moderator of the efficacy of cognitive training, as it fosters cognitive control and prefrontal activity [35]. Training motivation may be increased by a personalized context that links the goals of the training to everyday life [35]. Hence, as a naturalistic VR environment, such as a VR classroom, links goals of the training to a real-life situation, we should expect NFT and BFT taking place in a naturalistic VR environment to yield larger effects than training in 2D. The present study will investigate whether effects of a NIRS-based NFT are larger when the training is conducted in a naturalistic VR environment compared to a 2D setting.

Children with ADHD experience poor school performance [6–8] as well as a core deficit in self-control [3], that is, “the deliberate, conscious, effortful subset of self-regulation” [82]. However, aspects often neglected in prior studies include the effects of NFT and BFT on self-control and school performance. Depicting NFT and BFT as interventions that train the exertion of self-regulation in two domains, namely self-regulating an endogenous parameter and self-regulation of behaviour, it seems plausible to expect effects on and to assess self-control while investigating effects on the self-regulation of brain activity and behaviour. Furthermore, as poor school performance is related to difficulties in behaviour, EF, and self-control [8], and both NFT and BFT have been shown to improve behaviour and EF (e.g. [83, 84]), we should expect all three interventions administered in this study to improve school performance. Hence, it is vital to assess the effects of a NIRS-based NFT and an EMG-based BFT on school performance.

The present study is limited in that participants, parents, and the trainers administering the intervention are not blinded — even though an official debriefing of parents and children as well as communication of individual results will only take place after finishing the study, hence, after the follow-up test is completed. First, participants, parents, and trainers are not blinded due to time constraints that make it impossible to use both the NIRS machine and the EMG equipment simultaneously. Second, participants either wear or do not wear the HMD, and hence they will know whether it is the 2D or VR condition they belong to. Third, as measurements during training sessions require constant observation of the data being recorded, it is impossible to blind trainers for the kind of intervention administered. However, participants, parents, and trainers are informed that every participant receives a potent intervention. Hence, we hope that bias is reduced to a minimum.

We have presented the design and protocol for a randomized controlled trial on a NIRS-based NFT in a VR classroom for children with ADHD. In addition to assessing the effects of an NFT using this relatively new technology, and besides the fact that this is, to our knowledge, the first study examining differential effects of an NFT in children with ADHD in a 2D and a VR setting, we add the assessment of concepts that have rarely been considered in prior NFT studies to established measures.

### Trial status

The trial is ongoing.

## Abbreviations

ADHD: Attention-deficit/hyperactivity disorder
BFT: Biofeedback training
BRIEF: Behaviour Rating Inventory of Executive Function
C3-P: Conners 3 parent questionnaire (long form)
C3-T: Conners 3 teacher questionnaire (long form)
CFT: Culture Fair Test
CPT: Conner’s Continuous Performance Test
deoxy-Hb: Deoxygenated haemoglobin
dlPFC: Dorsolateral prefrontal cortex
DSM-5: Diagnostic and Statistical Manual of Mental Disorders, fifth edition
EEG: Electroencephalogram
EF: Executive function
EMG: Electromyogram
FERT: Questionnaire to assess relevant therapy circumstances
fMRI: Functional magnet resonance imaging
fNIRS: Functional near-infrared spectroscopy
HMD: Head-mounted display
HRQoL: Health-related quality of life
HRV: Heart rate variability
ISI: Interstimulus interval
KINDL-R: Questionnaire to assess HRQoL
LVD-M 2–4: Curriculum-based assessment of mathematics skills for Grades 2–4
MNI: Montreal Neurological Institute
NFT: Neurofeedback training
NIRS: Near-infrared spectroscopy
oxy-Hb: Oxygenated haemoglobin
RTC: Randomized controlled trial
SCP: Slow cortical potential
SCS-K-D: Brief Self-Control Scale
SD: Standard deviation
SDQ-Deu: Strengths and Difficulties Questionnaire, German version
SLRT-II: Lese- und Rechtschreibtest, an advanced version of the Salzburger Lese- und Rechtschreibtest (SLRT)
VFT: Verbal fluency task
VR: Virtual reality
